### Sample Size

The 2 largest and most similar studies [16,18], both commenced with a presearch correct answer rate of around 30% (29% and 32%) and a postsearch rate around 50% (50% and 46%). Using this as our basis, we wanted to be able to discriminate between the postsearch correct answer rate between each of the 3 time-constrained cohorts. Therefore, to derive the sample size, we estimated that the correct answer rates might vary evenly by 10 percentage points between each group, starting at no improvement. This creates 3 datasets with average correct answer rates of 30%, 40%, and 50% for the 3-, 6- and 9-min cohorts, respectively. Applying a 2-proportion statistical comparison (ie, a 2-sample, 2-sided equality) [66], between each pair of answer rates and setting statistical power to 90%, error rate to 5%, and equal sample sizes per cohort, the minimum sample size required is 514 per cohort, which equates to 32 people per cohort sitting 16 tasks or 96 people in total.

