### Task Order, System Rotation, and Task Timing

Task order and system rotation is set as per the table in Multimedia Appendix 4 for each participant to minimize confounding factors. The design is as follows:

A Latin square experimental design is constructed for 16 tasks and 16 participants to minimize the impact of user fatigue on specific tasks.To minimize task order effects, each column of the square is randomized.To incorporate a within-subject design across the system variable, 2 sets of the Latin square derived in (2) are required with alternating use of systems. The first tranche of 16 participants will start their first task with the state-of-the-art system, whereas the second tranche will start with BM25 system. In this way, across the 32 participants, each system will be used equally across all tasks and will experience the same task-order pattern.

The search time allowed for each task is controlled by applying a time limit for each task the participant performs. Participants are randomly assigned to 1 of 3 timing cohorts. The time constraint by task number is specified for each cohort in Multimedia Appendix 5. The rotation of task timing ensures that:

the maximum duration for search in stage 2 is fixed to 96 min for all participantseach task is conducted under all time constraints an equal number of times (32 per cohort)a within-subject design across the time constraint variable such that each participant performs 4 to 6 tasks per time constrainttask time constraints are applied in the same random order according to the task order rotation Latin square, specified above

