To assess the impact of time constraints on clinical decision quality (RQ-2), the analyses above will be repeated with a breakdown by time constraint category, that is, 3, 6 and 9 min. In addition, an analysis of time-outs by constraint category will be conducted to assess the impact of time constraints on task completion. Time-outs are defined as samples where at the postsearch answer stage (1) the task timer reaches the constraint duration and (2) the participant provides no evidence to support their answer. It is assumed that in a time-out scenario, the participant was unable to complete the task. Significant differences by time-constraint category will be analyzed using the chi-square analysis. An analysis of variance (ANOVA) will be performed across confidence, difficulty, participant-perceived time impact assessments (impact of time on answer, evidence capture, and stress), and search behaviors, such as SERP dwell time, number of queries issued, number of documents opened, and the quantity of evidence items selected. To gain an understanding of the impact of providing a time constraint on the decision-making process, both the average time to search and the average proportion of available search time used will be evaluated and compared for the different task-timing samples. Tombros et al [67] used this proportional figure as a further gauge of participant stress and it can be compared with the reported stress by the participants.

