To assess the impact of search engine performance on clinical decision quality (RQ-3), a similar set of analyses will be performed as that for RQ-1, except broken down by search system (state-of-the-art and BM25). In addition, the same ANOVA methods employed for time-constraint categories in RQ-2 analysis will be performed. In addition, an ANOVA will be performed across system categories and system time constraints to identify cases where system performance effects may matter most. The impact of search engine performance on clinical decision time (RQ-3) will also be assessed by evaluating the postsearch task completion times for those tasks that were completed (ie, relevant documents and/or evidence identified). This is measured in 2 ways: (1) search time only and (2) search time plus time spent filling in the answer form. Differences in search times between the systems will be assessed using the chi-square analysis. Finally, a participant-derived performance assessment of the 2 systems can be constructed by building a graded query relevance (QREL) listing (standard format for representing relevance assessments in IR), by query, based on all participants’ relevance ratings. Using this QREL, a recomparison of the 2 systems can be evaluated and compared using the formal TREC evaluation results to provide better insight into any changes observed (or not) in the clinical decision and timing results for the 2 systems.

There are a number of potentially confounding factors within the experimentation. A covariant analysis (repeated measure ANOVA) will be performed on the task number, task at total duration point (for fatigue), and time transitions (eg, 3-min task to 6-min task and 3-min task to 9-min task).

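### For correctness, RQ2 and RQ3 are analysed by separate pre/post tests within each time limit and each system; no stated analysis directly compares limits or systems using the within-subject crossing

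*Protocol article*

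**What the plan says.** The Study Aims pose RQ2 as the effect of time pressure on decision quality, and RQ3 as whether a better search system gives better and faster decisions. The Sample Size section states the aim for time: "we wanted to be able to discriminate between the postsearch correct answer rate between each of the 3 time-constrained cohorts". It assumes "average correct answer rates of 30%, 40%, and 50% for the 3-, 6- and 9-min cohorts, respectively" and uses a "2-sample, 2-sided equality" test of two proportions for each pair of rates.

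The section on task order, rotation and timing describes a "within-subject design across the time constraint variable such that each participant performs 4 to 6 tasks" under each limit. The two systems also alternate within participant.

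In Statistical Analyses, RQ1 correctness is tested presearch against postsearch with McNemar and sign tests, with a chi-square between professional groups. For RQ2, "the analyses above will be repeated with a breakdown by time constraint category, that is, 3, 6 and 9 min". For RQ3, "a similar set of analyses will be performed as that for RQ-1, except broken down by search system". Three other analyses bear on the point:

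- a chi-square by time-constraint category, in the sentences that follow the definition of a time-out;
- an ANOVA across systems and time limits, with no outcome named;
- a repeated-measures ANOVA for task number, fatigue and time transitions.

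The outcomes listed for the RQ2 ANOVA are confidence, difficulty, perceived time impact and search behaviours. Correctness is not among them.

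**The concern.** A pre/post test within a stratum asks whether searching changed the correct rate there. RQ2 and RQ3 ask whether the result differs between strata. Separate verdicts cannot answer that, and they can mislead in both directions. If the true gain is the same everywhere and moderate, chance will often make one stratum significant and another not, which reads as a time or system effect. If the gains differ but are all large, every stratum is significant and a real difference goes unexamined.

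The contrast for which the study was sized is therefore not the one that the analysis section specifies for correctness. If the chi-square by time limit is meant to cover correctness as well, it treats the answers at each limit as independent groups. Limit and system are in fact crossed within participant and question, so differences in question difficulty and participant ability stay in the error term.

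**Working it through.** **1. The plan's own figure.** Inputs from Sample Size: "setting statistical power to 90%, error rate to 5%, and equal sample sizes per cohort", with rates 30%, 40% and 50%. Unpooled formula: n = (1.960 + 1.282)² × [p₁(1−p₁) + p₂(1−p₂)] / (p₁−p₂)².

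- 40% v 50%: 10.507 × (0.24 + 0.25) / 0.01 = 514.9
- 30% v 40%: 10.507 × (0.21 + 0.24) / 0.01 = 472.8
- 30% v 50%: 10.507 × (0.21 + 0.25) / 0.04 = 120.8

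The stated 514 is reproduced by 40% v 50%, the most demanding pair. With 32 × 16 = 512 answers per limit, power for that pair is 89.7% (pooled formula, answers taken as independent). That power belongs to a direct contrast between limits.

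**2. Equal true gains, separate verdicts.** McNemar power is approximately Φ(d / √((c − d²)/n) − 1.96), where d is the net gain and c the share of discordant pairs. The documents give no c; 20–40% is assumed. There are n = 96 × 16 / 2 = 768 pairs per system and n = 512 per limit. With power p in each stratum, two verdicts conflict with probability 2p(1−p), and three are not unanimous with probability 1 − p³ − (1−p)³. Strata are treated as independent, which is a simplification because the same participants supply all of them.

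| True gain, equal in all strata | c | Power per system | Two systems conflict | Power per limit | Three limits disagree |
|---|---|---|---|---|---|
| 4 points | 20% | 70% | 42% | 53% | 75% |
| 4 points | 30% | 53% | 50% | 38% | 71% |
| 4 points | 40% | 42% | 49% | 30% | 63% |
| 5 points | 20% | 88% | 22% | 72% | 60% |
| 5 points | 30% | 72% | 40% | 55% | 74% |
| 5 points | 40% | 59% | 48% | 43% | 74% |
| 6 points | 20% | 96% | 7% | 87% | 35% |
| 6 points | 30% | 86% | 24% | 70% | 63% |
| 6 points | 40% | 75% | 37% | 58% | 73% |
| 10 points | 20% | >99% | <0.1% | 99.9% | 0.2% |
| 10 points | 30% | 99.9% | 0.1% | 98.8% | 3.7% |
| 10 points | 40% | 99.3% | 1.3% | 95.2% | 13.7% |

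**3. The protocol's own rates.** Take a presearch rate of 30%, postsearch rates of 30/40/50%, and assume that 10% of answers change from right to wrong. With n = 512 per limit, simulation gives rejection by McNemar in 5%, 99% and 100% of trials at 3, 6 and 9 min. The 6- and 9-min limits are both significant almost always. Their 10-point difference, which drives the 514, is not tested.

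**4. What an unpaired test would cost.** Simulations of 96 × 16 answers with rotated limits compared an unpaired test with one adjusted for participant and question. The SDs (logit scale) are assumptions.

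Three limits, log-odds step 0.2 per limit:

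| SD participant / question | Power, chi-square | Power, adjusted | Type I, chi-square | Type I, adjusted |
|---|---|---|---|---|
| 0 / 0 | 81% | 81% | 4.9% | 4.8% |
| 0.5 / 0.8 | 65% | 72% | 3.0% | 4.5% |
| 0.7 / 1.2 | 50% | 66% | 2.1% | 5.1% |
| 1.0 / 1.5 | 38% | 60% | 1.5% | 5.5% |

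In a separate simulation with participant SD 0.5 and question SD 1.5, power for 40% v 50% between limits was 93% unpaired and 97% adjusted. For a 5-point system difference (42.5% v 47.5%) it was 52% and 67%, with type I error of 1.8% and 5.8%.

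**The case against.** The strongest reply is that a between-limit comparison can be found in the document. The Sample Size section describes a two-proportion comparison of each pair of limits, and the chi-square by time limit stands in a paragraph that opens with decision quality under RQ2. For RQ3, the system-by-limit ANOVA is a combined analysis. It would therefore be wrong to infer that the plan has no cross-condition analysis at all. What remains is that none is stated to compare correctness: the chi-square follows directly on time-outs, the ANOVA names no outcome, and no test of the correct rate between the two systems is named.

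Three other stronger readings fail.

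- A reader might infer that the within-subject design is wasted. It is not. The rotation balances task, order, system and limit, which protects against confounding whatever test is used, and McNemar keeps the pre/post pairing.
- A reader might infer that ignoring the crossing inflates false positives. In the balanced rotation the unpaired test is conservative, so the harm is lost power. At the planned 40% v 50% difference even the unpaired test stayed above the 90% target in the simulation shown.
- A reader might take 50% and 75% as the usual rate of conflicting verdicts. Those are the mathematical maxima of the two formulas, reached when each test has about 50% power. At a 10-point gain, the step used for planning, conflict is rare.

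Stratum-specific pre/post rates also serve a stated purpose, comparison with the earlier study whose method is largely replicated.

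**Conclusion.** The concern stands in this form: for correctness, the tests named for RQ2 and RQ3 do not test the differences that those questions ask about, and the contrast used for sizing is not carried into the analysis section. This follows from the text and needs no numerical assumption.

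The size of the consequence does depend on assumptions. With 20–40% discordance and equal gains of 4–6 points, verdicts conflict in about 7–50% of trials for two systems and 35–75% for three limits, falling to about 0–1% and 0–14% at 10 points. At the planned rates the risk is the opposite one: two significant strata and an untested 10-point difference. The loss from an unpaired test is nil at zero participant and question variance. It reaches about 15 power points for a 5-point system contrast at a question SD of 1.5 logits; part of that gap may reflect the adjusted test's slightly high type I error of 5.8%. The conservatism also presumes a balanced rotation, which the planned discarding of samples without evidence or relevant documents may disturb.

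**What to change.** State that the correctness analyses for RQ2 and RQ3 are direct contrasts from one model of postsearch correctness. Use mixed-effects logistic regression with fixed effects for time limit, system, their interaction and presearch correctness on the same question, and random effects for participant and question. Name a fallback if it does not converge (GEE or conditional logistic regression, still accounting for participant and question). Read RQ2 from the limit contrasts, RQ3 from the system contrast, and where system performance matters most from the interaction.

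Say whether the chi-square by time limit covers time-outs only, and name the outcome of the system-by-limit ANOVA or let the interaction replace it. Keep the stratum-specific pre/post rates and McNemar results as description and for comparison with the earlier study.

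The cost is wording and programming; no new data are needed, and the article reports 69 of 96 participants enrolled, so the change could precede the results. There is a small downside: extra modelling work and model assumptions, with only 16 questions from which to estimate the variation between questions.

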The participant must complete the same 16 tasks in the same order as stage 1; however, the participant must now use Taskiir to help them answer the question and to find evidence to support their answer. Evidence is collected by the participant selecting text, images, or both from the source documents they read. The time allocated to search for each task is set according to the timing cohort the participant belongs to and will be one of 3, 6, or 9 min. The participant is told of the time allocation at the start of each question and a minute-by-minute countdown timer is always visible to the participant; warnings are given 30 seconds before time-out. At time-out, the screen is blocked, and the participant is taken to the task completion screen to enter their final details. Other methods of communicating the time limit were trialed during development of the system. In the end, the above method was chosen because it provided a balance between (1) making the participant aware of the time allocated for each question, (2) avoiding time anchoring (where the participant incorrectly assumed all questions are allocated the same time as the first question), (3) keeping them updated with the time remaining so they do not run out of time without warning, and (4) not distracting the participant with time information (eg, using a second-by-second countdown timer that diverted too much attention away from the task).

As this is the first such study measuring the impact of time variation, a few time limits covering a wide range are required to generate significant differences in the outcomes. A useful starting point to establish these time limits is the average completion time of 6.1 min per question, reported in the Westbrook study [33]. From the same study, the SD, based on the average completion times for each of the 8 questions, across 2 systems, is 3.1 min. Therefore, time limits are set at the average question answer time (6 min) and approximately 1 SD either side of this (3 and 9 min). These limits should induce time pressures for 84% of questions with a 3-min time limit, 50% of questions with a 6-min time limit, and 16% of questions with a 9-min time limit. From previous studies, realistic answer timeframes for busy clinicians should be below 5 min [3,15,35], so the 3 proposed time limit cohorts will encompass this pragmatic indicator of search time suitability.

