### Custom Search System

A custom search engine and interface, together called Taskiir, is employed for the evidence search process (see Figure 2). Similar to normal commercial search engines, Taskiir allows the participant to write their query and perform a best match search of documents in the corpus. A snippet, highlighting matching query terms, is then provided in the SERP, which shows up below the query. Users can then select documents of interest to view the full text. While viewing the full text document, the participant can also select (with their mouse) any text or graphics that they want to use as evidence for their final answer. The participant can view their evidence or complete the task at any time. Instructions on using the system are provided on each page, and a mandatory walk-through tutorial is provided before starting the study.

To investigate the impact of search system effectiveness on clinical decision making (RQ2), Taskiir utilizes 2 search algorithms: (1) A state-of-the-art system, which is an improved version of the TREC 2015 CDS Task A winning system [61]. The TREC 2015 CDS track was targeted to identify the state-of-the-art IR system because the topics in Task A were of a similar clinical nature to the Westbrook tasks and the search corpus was the same as that used in this study. The 2 improvements made over the winning system include the removal of negated Unified Medical Language System (UMLS) terms from the UMLS query expansion terms as well as a change to the pseudorelevance feedback term weighting (from 0.75 to 0.5). All improvements resulted from tuning parameters on the CDS 2014 test collection and testing on the 2015 collection to avoid data overfitting. (2) A baseline document retrieval system consisting of a BM25 algorithm, which is a widely adopted best-match retrieval method. It is the default, out-of-the-box method employed by many search engines, including the very popular Elasticsearch (Elasticsearch BV) [63] and Lucene (Apache) systems [64]. The parameters were set to default values (K=1.2; b=0.75).

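### The effect of the time limits on task completion is judged by time-outs alone, so the time-out rate can fall from 3 to 9 min without any change in the share of tasks completed

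*Protocol article*

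**What the plan says.** All of the following is in the protocol article.

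- Statistical Analyses, RQ-2 paragraph: "an analysis of time-outs by constraint category will be conducted to assess the impact of time constraints on task completion". A time-out is a sample where, at the postsearch answer stage, "1) the task timer reaches the constraint duration and (2) the participant provides no evidence to support their answer". The reading to be given is stated: "It is assumed that in a time-out scenario, the participant was unable to complete the task". So is the test: "Significant differences by time-constraint category will be analyzed using the chi-square analysis". The RQ-2 text names no other measure of completion.
- Custom Search System: "The participant can view their evidence or complete the task at any time".
- In Stage 2 (Procedures): "These limits should induce time pressures for 84% of questions with a 3-min time limit", with 50% and 16% given for the 6-min and 9-min limits.
- Statistical Analyses, RQ-1 paragraph: samples with neither evidence captured nor a relevant document marked are dropped from the correct answer rate.
- Statistical Analyses, RQ-3 paragraph: decision times are compared for "those tasks that were completed (ie, relevant documents and/or evidence identified"). This meaning of completion has no timer condition, and either a document or evidence satisfies it.

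**The concern.** Whether a failed search counts as non-completion depends on the limit, which is the factor under test. A participant who would abandon a fruitless search at minute 7 is stopped by the timer at 3 or 6 min and is a time-out. At 9 min the same participant leaves before the timer and is not. A longer limit makes the timer condition harder to meet, so the time-out rate drifts down for a reason unrelated to whether anything was found.

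The plan reads a time-out as inability to complete the task. A falling rate would therefore be reported as longer limits letting clinicians finish more tasks, when part or all of the fall could come from uncounted early stops. Early stops with neither evidence nor a marked document also leave the correct answer rate through the discard rule, and they are not completed tasks under RQ-3. No stated analysis reports how many there are at each limit.

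**Working it through.** **The protocol's own figures.** The limits are set at about the mean completion time and one SD either side. A normal distribution with mean 6 and SD 3 has 84.1%, 50.0% and 15.9% above 3, 6 and 9 min, so the stated 84/50/16% reproduces. With the unrounded 6.1 and 3.1 the shares are 84.1%, 51.3% and 17.5%.

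**Answers per limit.** 96 participants × 16 tasks / 3 limits = 512.

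**Model.** Two quantities are assumptions, because the protocol gives neither:
- q, the share of tasks that end without evidence, held equal at all three limits so that completion by this measure does not change;
- e, the share of those non-finders who stop of their own accord; the rest stay until the timer ends the task.

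For voluntary stopping times I borrow s = 0.84, 0.50, 0.16 as the share still searching at 3, 6 and 9 min. This is an illustration, since those figures describe question completion times.

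Time-out rate at a limit = q × [(1 − e) + e × s].

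Ratio of 3 min to 9 min = (1 − 0.16e) / (1 − 0.84e), which does not depend on q. For example, at e = 0.5 it is 0.92 / 0.58 = 1.59.

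Expected chi-square = 512 × Σ(rate − mean rate)² / [mean rate × (1 − mean rate)], on 2 df, with answers treated as independent.

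Results for q = 20%, where true non-completion is 20% at every limit:

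| e | Time-outs at 3 / 6 / 9 min | 3:9 ratio | Chance that the chi-square test reaches 5% |
|---|---|---|---|
| 0 | 20.0 / 20.0 / 20.0% | 1.0 | 5% |
| 0.25 | 19.2 / 17.5 / 15.8% | 1.22 | 23% |
| 0.5 | 18.4 / 15.0 / 11.6% | 1.59 | 78% |
| 0.75 | 17.6 / 12.5 / 7.4% | 2.38 | 99.6% |
| 1 | 16.8 / 10.0 / 3.2% | 5.25 | about 100% |

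Two rows worked through:
- e = 0.25: 512 × 2 × 0.017² / (0.175 × 0.825) = 2.05, p about 0.36.
- e = 0.5: 512 × 2 × 0.034² / (0.15 × 0.85) = 9.3, p about 0.01.

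A smaller q weakens the signal. At q = 10% and e = 0.5 the rates are 9.2 / 7.5 / 5.8%, chi-square about 4.3, p about 0.12. At q = 10% and e = 1 they are 8.4 / 5.0 / 1.6%, chi-square 24.9, p about 4 × 10⁻⁶.

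**The two meanings of completion side by side.** For a task that ends without evidence:

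| How it ended | Document marked relevant? | RQ-2 time-out | RQ-3 completed | Kept in correct rate |
|---|---|---|---|---|
| Timer | Yes | Yes | Yes | Yes |
| Timer | No | Yes | No | No |
| Early stop | Yes | No | Yes | Yes |
| Early stop | No | No | No | No |

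The first row is unable to complete under RQ-2 and completed under RQ-3. The last row is counted by none of the three.

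**The case against.** The best defence is that the time-out rate is a cause-specific measure. A task that the timer ended with no evidence is one where the limit can plausibly have caused the failure, whereas someone who leaves at minute 7 of 9 was not stopped by the limit. That is a fair reason to keep the rate. It does not justify using it as the only measure of the effect on completion, because the plan equates a time-out with an uncompleted task and leaves the remaining uncompleted tasks untallied.

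Participants are also told that they must use the system to find evidence, so stopping early without any departs from the instructions and may be rare. This stands: at e = 0 the artefact disappears.

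Three stronger readings are tempting, and the protocol does not support them.

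- A reader might infer that the chi-square is bound to be highly significant, with a five-fold fall. That needs every non-finder to quit on the 84/50/16% schedule. Those percentages come from average completion times per question in an earlier study, not from give-up times.
- A reader might infer that early stops appear in no analysis. The RQ-2 ANOVA on the quantity of evidence items states no exclusion and would include them as zeros, and the comparisons of search time bear on them too. Those with a marked document stay in the correct rate and are completed under RQ-3. The ANOVA is not, however, offered as a measure of completion.
- A reader might infer that RQ-3 is defective without a completion rate by engine. RQ-3 asks about better and faster decisions, and for it "the same ANOVA methods employed for time-constraint categories in RQ-2 analysis will be performed", which covers evidence quantity. A completion rate by engine would be a useful addition; its absence contradicts nothing.

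**Conclusion.** The point holds as a fault of definition. The only stated RQ-2 measure of task completion includes a condition that becomes harder to meet as the limit lengthens, so it can show improvement from 3 to 9 min when completion has not changed. This is so whenever some non-finders stop early (e above 0) and some of those stops fall between the limits.

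The size is unknown. On the illustrative stopping times, the 3:9 min ratio runs from 1.0 to 5.25 as e goes from 0 to 1, and is 1.2 to 1.6 for e between 0.25 and 0.5. Significance is therefore possible but not assured. The time-out analysis is also an addition to the main RQ-2 comparison, which is the correct answer rate by limit. The point affects what may be said about completion under time pressure and leaves the main RQ-2 analysis in place.

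**What to change.** In the RQ-2 paragraph of Statistical Analyses:

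1. Define a task as not completed when neither a relevant document nor evidence was identified, whatever the timer shows. This matches the RQ-3 meaning, so one definition serves both questions. Using absence of evidence alone would create a new conflict with RQ-3.
2. Compare the proportion not completed between 3, 6 and 9 min over all allocated tasks, before any discard.
3. Split non-completers into those cut off by the timer and those who stopped early, and show both at each limit.
4. Keep the time-out rate as a descriptive, cause-specific component, and state how many time-outs had a document marked, since these are completed under the common definition.

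Optionally, report the same completion proportion by search system beside the RQ-3 comparison of completion times, because that comparison is restricted to completed tasks.

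The cost is analysis wording and one extra tabulation. Timings, document ratings and evidence are already captured for every task, so no new data or participants are needed. The likely price is a less striking time-out contrast.
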